### Sample size

2.7

The null hypothesis of this study is that there will be no differences in the improvement of acute neck pain between the experimental group and control group after the additional use of NRT by the experimental group, and the null hypothesis will be tested using analysis of covariance as the primary analysis. The significance level (*α*) was set at 0.05 (two-tailed), type 2 error (*β*) at 0.2, and power at 90% to calculate the sample size. The sample size was determined with reference to a previous pilot study. The Cohens’ *d* was 0.63, and the correlation between the baseline and endpoint measurements was assumed to be 0.5. A total of 41 participants were needed per group. Based on a 30% potential withdrawal rate, the target number of participants was set to 60 for each group.

### Allocation and concealment

2.8

The same number of patients will be assigned to each groups using a randomization table generated by a statistician that is not directly involved in the study. Block randomization will be used, and the size of each block will be randomly set to 2, 4, or 6. The assignment results will be sealed in an envelope and stored in a double-locked safe until immediately before the initiation of the treatment for the participants who sign the consent form. After opening the envelope, no one can alter the assignment results, and the random number displayed inside the envelope will be assigned to the patient and recorded in the electronic medical records. Only investigators registered for the trial can screen, enroll, and assign a random envelope to the participants.

### Blinding (masking)

2.9

Due to the nature of the intervention, it will be impossible to blind the participants and the physician, so we will blind the assessor, who is not involved in the screening or intervention, during the outcome measurements.

### Data collection, management, and analysis

2.10

The standard operating procedure (SOP) will be provided to the investigators, including the assessor and physicians, and they will be trained for the assessments and data entry based on the SOP. Only the investigator who is responsible for data management can access the data recorded on the case report form. The investigators will be in touch with the patients for 12 weeks for the follow-up assessments, and the patients will be allowed to ask study-related questions at any time during the study period by contacting the investigator through the investigator's contact information provided prior to the beginning of the study. Patients who have to discontinue the study will be followed up upon providing consent for follow-up.

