### Criteria for discontinuing

2.4

1.In the case of participant who have been found to have a disease that could affect the decision of the study result that was not discovered at baseline assessment.2.During the clinical study period, when the participant or participant's legal representative requests to discontinue the study, or the participant withdraws consent.3.Confirmation during treatment.4.Existence of a problem in performing medical or oriental medical treatment for neck pain.5.In case the continuation of participation is not appropriate due to the judgment of the researcher.

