### Statistical methods

2.11

In this study, both the intention-to-treat and per-protocol analyses will be performed, with intention-to-treat as the primary analysis. In the per-protocol analysis, participants who receive at least three sessions of treatment will be analyzed separately. The NRT + IKMT group and IKMT group will be compared, and the aim is to evaluate the superiority of NRT + IKMT.

Missing values will be processed through a mixed model for repeated measures in the primary analysis, and multiple imputations and the last observation carried forward will be performed for sensitivity analysis. For the Kaplan-Meier curve and log-rank test, the patients who drop out will be right censored, and regarding intermittent censoring, we will assume that no event occurred during the specified time period.

The sociodemographic characteristics of the participants and treatment expectancy will be evaluated by group. Continuous variables will be presented as mean (standard deviation) or median (quartile), and the two groups will be compared using the Student *t* test or Wilcoxon-rank sum test depending on the distribution pattern. Categorical variables will be presented as frequency (%) and will be analyzed using chi-square test or Fisher's exact test.

The endpoints of this clinical trial are the changes in the continuous outcomes (NRS, VAS, NDI, SF-12, ROM, PCL-5-K) at each time point from the baseline. A linear mixed model will be used as the primary analysis, and a random intercept model, which includes subject the random effects. Fixed effects will include baseline outcomes and clinically important covariant factors that are statistically significantly differ between groups at baseline as the covariates. In addition, time, group allocation, and the time and group interaction will be included in the model to examine the differences in the amount of change over time between the groups. For sensitivity analysis, we will perform analysis of covariance on the multiple imputations and last observation carried forward sets with the same covariates as those in the primary analysis and the group set as the fixed factor.

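### Outcome follow-up after investigator-driven discontinuation depends on consent for follow-up, which weakens, without contradicting, the intention-to-treat primary analysis

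*Protocol article*

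**What the plan says.** Protocol article, section 2.4 (Criteria for discontinuing), gives five reasons in one list. Three matter here:

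- Criterion 1 covers a participant "found to have a disease that could affect the decision of the study result that was not discovered at baseline assessment".
- Criterion 2 covers a request to stop by the participant or legal representative, "or the participant withdraws consent".
- Criterion 5 reads: "In case the continuation of participation is not appropriate due to the judgment of the researcher".

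Section 2.10 sets a single follow-up rule, whichever criterion applied: "Patients who have to discontinue the study will be followed up upon providing consent for follow-up".

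The context is as follows:

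- Table 1 puts consent on Day 1, randomisation on Day 2 and scheduled assessments out to 12 weeks.
- Section 2.9 says that "it will be impossible to blind the participants and the physician, so we will blind the assessor".
- Section 2.11 states that "both the intention-to-treat and per-protocol analyses will be performed, with intention-to-treat as the primary analysis", and that "Missing values will be processed through a mixed model for repeated measures in the primary analysis".

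**The concern.** An intention-to-treat comparison needs outcomes from everyone randomised, including those who stop treatment or turn out to be ineligible. Criteria 1 and 5 are not the patient's choice, yet section 2.10 treats them like a withdrawal of consent: assessment goes on only if consent for follow-up is given.

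These criteria can act after Day 2, when the arm is known to the patient and the treating physician. Criterion 1 is tied to prognosis by its own wording, because its test is whether the disease might influence the result. Criterion 5 has no objective test. The patient who is then asked about follow-up also knows the arm. Missing outcomes could therefore be related to arm and to prognosis together.

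The mixed model is valid if data are missing at random given what was observed. A judgement about a course not yet recorded falls outside that assumption. A later analysis plan cannot recover outcomes that were never collected, so the rule belongs in the protocol.

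**Working it through.** **1. The plan's own figure.** Section 2.7 gives d = 0.63, correlation r = 0.5, two-sided alpha 0.05 and power 90%. With analysis of covariance, n = 2(1 − r²)(1.960 + 1.282)² / d² = 2 × 0.75 × 10.51 / 0.397 = 39.7, so 40 per group; the t-based calculation gives 40.7, so 41 as stated. Allowing for 30% loss, 41 / 0.70 = 58.6, so 59 against the stated 60. The sample size reproduces, and this point changes none of it. The issue is bias, not power.

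**2. Bias with no help from earlier scores.** Assumptions not in the document: 6 of 60 NRT and 2 of 60 control patients are lost this way, and their Day 5 change would have been 2 points worse than that of the patients retained.

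- Bias = (6/60 − 2/60) × 2 = 0.133 points.
- With an assumed SD of 2, 0.133 / 2 = 0.067 SD, and 0.067 / 0.63 = 10.6% of the planned effect.
- If the losses balance between arms, the bias is 0.

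**3. What the mixed model recovers.** Table 1 schedules neck-pain NRS on every treatment day. Assume that three daily values (Days 2 to 4) were observed before the loss, with equal within-patient correlation ρ between days. A random-intercept model carries forward a fraction k = 3ρ / (1 + 2ρ) of the mean earlier deficit. At ρ = 0.5, k = 1.5 / 2 = 0.75. Bias left = (4/60) × (2 − k × mean earlier deficit).

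| Course of the deficit | Mean over Days 2–4 | Bias left, ρ = 0.5 | Range, ρ = 0.7 to 0.3 (k = 0.875 to 0.5625) |
|---|---|---|---|
| Present throughout at 2 points | 2.0 | (4/60) × 0.50 = 0.03 | 0.02 to 0.06 |
| Builds linearly (0.5, 1.0, 1.5, then 2) | 1.0 | (4/60) × 1.25 = 0.08 | 0.08 to 0.10 |
| Abrupt after the last value, or no post-baseline value | 0 | (4/60) × 2 = 0.13 | 0.13 |

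**4. Other loss rates, in one arm only, with no recovery.** For a share p lost with outcomes g SD worse, bias = p × g. The standard error is √0.75 × √(1/60 + 1/(60(1 − p))).

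- p = 5%, g = 0.5: bias 0.025 SD; two-sided type I error 0.053, which is negligible.
- p = 10%, g = 0.5 to 1.0: bias 0.05 to 0.10 SD (8% to 16% of 0.63). The standard error is 0.162 and type I error 0.06 to 0.09.

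**5. Later outcomes.** After Day 5 only discharge and 12 weeks remain. Outside the case where discharge falls on Day 4 or 5, NDI, SF-12 and PCL-5-K have one value before discharge (Day 2) and PGIC has none. The model then has little or no earlier course to draw on. The analysis of time to halving of the NRS right-censors dropouts, so the same losses enter there too.

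**The case against.** The strongest reply is that the sentence in section 2.10 is a provision for following discontinued patients, and that the same section keeps investigators in touch with patients for 12 weeks. The article does not say when or how consent for follow-up is obtained. It could be part of the entry consent form, which is not available here. A reader might infer that a fresh consent is required at discontinuation. That is the natural reading, since patients have already consented to a schedule that runs to 12 weeks, but it remains an inference.

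A reader might also infer that arm-aware investigators decide who is discontinued, and that the NRT arm will lose more patients. Section 2.4 says only the researcher, and section 2.9 names the physician as unblinded; the link between the two is plausible but not stated. Differential detection is weaker still. Controls also receive a manual therapy (Chuna), both arms have symptom checks at every visit, and the contrast is four extra sessions of about 10 minutes. Nothing in the document supports 6 versus 2 as a forecast.

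Finally, it would be too strong to say that the mixed model cannot help. As shown, it recovers part of the loss whenever earlier scores already reflect the deficit.

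What stands is that the article states one conditional rule for all reasons and nowhere makes continued assessment the default after an investigator-driven discontinuation. This is a stated rule, not a detail left to another document.

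**Conclusion.** The point holds as a weakness in data collection, worth correcting but modest in size. A reader might conclude that the plan contradicts its own intention-to-treat analysis. The documents do not support that: no section removes discontinued patients from the intention-to-treat set or discards data already collected.

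For the Day 5 primary endpoint the risk is limited by the short inpatient window from Day 2 to Day 5 and by the repeated NRS values. In the assumed 6 versus 2 scenario the overstatement is at most about 0.13 points (0.07 SD at an assumed SD of 2), and less if the deficit was already visible. It is larger for discharge and 12-week outcomes, though the document gives no basis for a figure there.

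The 30% allowance in section 2.7 (0.30 × 60 = 18 per arm) should not be read as an estimate of this loss. It covers withdrawal from all causes and is neither a Day 5 rate nor a rate for criteria 1 and 5.

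**What to change.** In sections 2.4 and 2.10, separate ending study treatment from ending data collection:

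- State that discontinuation for investigator-driven reasons does not end outcome assessment. The Day 5, discharge and 12-week assessments continue under the original consent unless the patient withdraws consent to data collection.
- Keep the consent-for-follow-up condition only for patients who withdraw under criterion 2. Deleting it outright would promise follow-up of people who have withdrawn consent.
- Handle late-found ineligibility as a protocol deviation in the per-protocol set, which section 2.11 at present describes only by the number of sessions received.
- Clarify criterion 3, which names a confirmation without saying of what, before applying the rule to it.

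The cost is a few sentences in the protocol and, if the entry consent does not already cover it, one in the consent form. The visits are already scheduled, so the downside is a few additional assessments in patients who have stopped treatment. The change concerns data collection only and alters no rule on when treatment stops.

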### Statistical methods

2.11

In this study, both the intention-to-treat and per-protocol analyses will be performed, with intention-to-treat as the primary analysis. In the per-protocol analysis, participants who receive at least three sessions of treatment will be analyzed separately. The NRT + IKMT group and IKMT group will be compared, and the aim is to evaluate the superiority of NRT + IKMT.

Missing values will be processed through a mixed model for repeated measures in the primary analysis, and multiple imputations and the last observation carried forward will be performed for sensitivity analysis. For the Kaplan-Meier curve and log-rank test, the patients who drop out will be right censored, and regarding intermittent censoring, we will assume that no event occurred during the specified time period.

The sociodemographic characteristics of the participants and treatment expectancy will be evaluated by group. Continuous variables will be presented as mean (standard deviation) or median (quartile), and the two groups will be compared using the Student *t* test or Wilcoxon-rank sum test depending on the distribution pattern. Categorical variables will be presented as frequency (%) and will be analyzed using chi-square test or Fisher's exact test.

The endpoints of this clinical trial are the changes in the continuous outcomes (NRS, VAS, NDI, SF-12, ROM, PCL-5-K) at each time point from the baseline. A linear mixed model will be used as the primary analysis, and a random intercept model, which includes subject the random effects. Fixed effects will include baseline outcomes and clinically important covariant factors that are statistically significantly differ between groups at baseline as the covariates. In addition, time, group allocation, and the time and group interaction will be included in the model to examine the differences in the amount of change over time between the groups. For sensitivity analysis, we will perform analysis of covariance on the multiple imputations and last observation carried forward sets with the same covariates as those in the primary analysis and the group set as the fixed factor.

To compare the number of changes for each outcome within the study period (during treatment and the entire study period) in both groups, we will calculate the areas under the curve at each time point following randomization. The time from randomization to the point at which NRS reduces by more than half of the score will be compared using the Kaplan-Meier survival analysis, and the curves will be compared using a log-rank test. Additionally, we will use the Cox Proportional Hazard Model to compare hazard ratios. We will perform subgroup analyses and compare the degree of pain improvement between the NRT + IKMT group and the IKMT group.

The significance level will be set at .05 for all analyses. All statistical analyses will be performed using the SAS 9.4 (© SAS Institute, Inc., Cary, NC) or R version 4.1.1 (© The R Foundation for Statistical Computing) software, with the statistical significance set at *P* < .05.

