**Method::**

This study will use a two-armed, parallel, assessor-blinded randomized controlled trial design and will be conducted in the Daejeon Jaseng Hospital of Korean Medicine in South Korea. One hundred twenty patients will be recruited and randomized into an integrative Korean medicine treatment (IMKT) + NRT group and IMKT group in a 1:1 ratio. The primary outcome is a change in the numeric rating scale for neck pain immediately after treatment on hospital day 5 compared to those at baseline. The secondary outcomes are numeric rating scale for radiating arm pain, visual analogue scale for neck pain and radiating arm pain, cervical active range of motion, neck disability index, Patient Global Impression of Change, Short Form-12 Health Survey, and Posttraumatic Stress Disorder Checklist for DSM-5.

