#### Experimental group: IKMT + NRT

2.3.1

For the experimental group, four sessions of NRT will be administered from hospital day 2 to 5, and IKMT will be administered daily. Each session of NRT will last for about 10 minutes.

During the NRT, the patient will be seated, and the therapist will apply pressure to the cervical treatment point while firmly supporting the patient's head and progressively extending the neck to move the joint. The therapist will apply pressure to the posterior neck with the thumb and other fingers while supporting the occipital region with the dorsum of the hand.

With the patient seated on a chair, the therapist will place the thumb and index finger on the areas around the articular pillar in the upper cervical region with tense muscles or on the acupoints GB20, BL10, GB21, or SI15; support the back of the patient's head with the 1^st^ and 2^nd^ metacarpal bone; and place the other hand on the patient's forehead. Then, light flexion and extension will be repeated within the ROM of the cervical spine without pain. The weight of the patient's head will add weight to the hand supporting the head and, thus, will transfer pressure to the thumb and index finger, and compression and relaxation will be repeated based on the transferred pressure. During the treatment, the therapist will comfort the patient by assuring them that the treatment does not cause pain so that the patient can relax the neck muscles. Once the targeted area is adequately flexed and extended over a sufficient period of time, the pressure points will be moved to the central and lower neck to repeat the procedure. The range of cervical extension increases at the lower neck area (Figure S1, Supplemental Digital Content).

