### Participant timeline

2.6

At the screening visit, the participants will be enrolled after signing a written consent form, and those who qualify per the inclusion/exclusion criteria will proceed with the trial. The detailed timeline is shown in Table 1.

**Table 1 T1:** Schedule of study.

Time point	Study period						
	Screening	Active treatment				Follow-up	
	Day 1 (visit 1)	Day 2 (visit 2)	Day 3 (visit 3)	Day 4 (visit 4)	Day 5 (visit 5)	Discharge (visit 6)	12 wks (visit 7)
Enrolment							
Eligibility screening	○						
Written informed consent	○						
Sociodemographic hic characteristics	○						
Information about accident	○						
Randomized allocation		○					
Credibility and expectancy questionnaire		○					
Intervention							
IKMT + NRT	Δ (only IKMT)	○	○	○	○	Δ (only IKMT)	
IKMT	○	○	○	○	○	○	
Assessment							
Check symptoms and Med change	○	○	○	○	○	○	○
NRS for neck pain	○	○∗	○∗	○∗	○∗	○	○
VAS for neck pain		○∗	○∗	○∗	○∗	○	
Neck ROM		○∗	○∗	○∗	○∗	○	
NRS for arm pain		○∗	○∗	○∗	○∗	○	○
VAS for arm pain		○∗	○∗	○∗	○∗	○	
NDI		○		○†		○	○
SF-12		○		○†		○	○
PGIC				○†		○	○
PCL-5-K		○		○†		○	○
Adverse events		○	○	○	○	○	○

If Day 5 (visit 5) and day of discharge are the same, then the assessment for Day 5 (visit 5) could be replaced by discharge assessment. The follow-up visit at 12 wks after registration will have a time window of ± 14 days. F/U = follow-up, IKMT = integrative Korean medicine therapy, NDI = neck disability index, NRS = numeric rating scale, NRT = non-resistance technique, PCL-5-K = post-traumatic stress disorder checklist for DSM-5, PGIC = patient global impression of change, ROM = range of motion, SF-12 = 12-item short-form health survey, VAS = visual analogue scale.

∗ Additional evaluation after treatment.

† Investigate only if Day 4 ad 5 (visit 4, 5) and day of discharge are the same.

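### The primary model is labelled both MMRM and random intercept; the random intercept misfits visits minutes to 12 weeks apart and can inflate the group-by-time test and, if variance differs by visit, the Day 5 test

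*Protocol article*

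**What the plan says.** Section 2.11 (Statistical methods) gives two descriptions of one primary analysis. On missing data it says: "Missing values will be processed through a mixed model for repeated measures in the primary analysis". On the model itself it names a linear mixed model and "a random intercept model, which includes subject the random effects". The fixed effects are baseline and selected covariates, and "time, group allocation, and the time and group interaction will be included in the model". No residual covariance structure, robust standard error or degrees-of-freedom method is named.

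The abstract sets the primary outcome as the "change in the numeric rating scale for neck pain immediately after treatment on hospital day 5 compared to those at baseline".

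Table 1 (Section 2.6) schedules neck-pain NRS on Days 1 to 5, at discharge and at 12 weeks. Days 2 to 5 carry a footnote: "Additional evaluation after treatment". Section 2.3.1 adds: "Each session of NRT will last for about 10 minutes". For the last visit the Table 1 note reads: "The follow-up visit at 12 wks after registration will have a time window of ± 14 days".

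**The concern.** A random intercept with independent residuals has two variance parameters. It therefore treats two scores from either side of a single session as no more alike than a Day 5 score and a 12-week score. It also assumes the same spread of scores at every visit.

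Two inferences depend on this. One is the group-by-time test, which Section 2.11 includes to compare change over time between groups. The other is the Day 5 post-treatment contrast, which serves the primary outcome. If the assumed covariance is wrong, either test may reject too often when NRT adds nothing. The two labels also leave a reader unsure which covariance the trial has committed to.

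**Working it through.** **The plan's own figure.** Section 2.7 gives d = 0.63, r = 0.5, two-sided alpha 0.05 and 90% power.
- ANCOVA formula: n = 2(z₀.₉₇₅ + z₀.₉₀)²(1 − r²)/d² = 2 × (1.960 + 1.282)² × 0.75/0.3969 = 39.7, so 40 per group.
- The noncentral-t version gives 41 (power 90.2%), as stated.
- 41/(1 − 0.30) = 58.6, so 59; the plan rounds to 60.

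This is a single-time-point calculation. It does not involve the covariance between post-baseline visits.

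**What the model implies.** With subject variance σ_b² and residual variance σ_e²:
- variance at every visit = σ_b² + σ_e²
- correlation of any two visits = σ_b²/(σ_b² + σ_e²)

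**Which inference is affected, and how.** Take balanced data with T post-baseline visits, and let v be the average variance and c the average between-visit covariance, both after baseline adjustment.
- The within-subject mean square estimates v − c. The between-subject mean square divided by T estimates [v + (T − 1)c]/T.
- Solving gives σ_b² = c and σ_b² + σ_e² = v.
- The standard error of the group difference at one visit is therefore close to √(2v/n). It depends on the pooled variance, not on how correlation decays, and it is too small when variance at Day 5 exceeds the average.
- The group-by-time F test divides by v − c as if it applied to every pair of visits. Decaying correlation breaks that directly.

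**Simulation under no treatment effect.** 41 per arm, complete data, 4000 replicates. Baseline is Day 2 before treatment. There are nine post-baseline assessments: after treatment on Day 2, before and after on Days 3 to 5, discharge, and 12 weeks. Monte Carlo standard error at 5% is √(0.05 × 0.95/4000) = 0.3 points.

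Assumed, not from the documents:
- Correlation: equal at 0.5; stronger decay, 0.2 + 0.7·exp(−lag/4 days); or milder decay, 0.35 + 0.5·exp(−lag/6 days).
- SD: constant at 2; growing from 1.3 at baseline to 2.0 at Day 5 and 2.4 at 12 weeks; or rising to 2.2 at Day 5 and falling to 2.0 at 12 weeks (peak).
- Discharge near Day 8.

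Under stronger decay the baseline-to-Day 5 correlation is 0.2 + 0.7·exp(−3.02/4) = 0.53, close to the plan's 0.5.

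RI = random intercept; UN = unstructured equivalent (Day 5 ANCOVA, Hotelling T² for the interaction). The SE column is mean model SE over empirical SD.

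| Correlation | SD | Day 5, RI | SE ratio, RI | Day 5, UN | Group×time, RI | Group×time, UN |
|---|---|---|---|---|---|---|
| equal | constant | 4.9% | 0.383/0.382 = 1.00 | 5.1% | 4.7% | 4.9% |
| equal | growing | 6.5% | 0.358/0.388 = 0.92 | 5.0% | 5.7% | 4.8% |
| equal | peak | 7.3% | 0.377/0.419 = 0.90 | 4.8% | 5.7% | 5.5% |
| stronger decay | constant | 4.6% | 0.361/0.371 = 0.97 | 4.5% | 8.5% | 5.0% |
| stronger decay | growing | 7.1% | 0.346/0.374 = 0.93 | 5.3% | 9.4% | 4.0% |
| stronger decay | peak | 8.7% | 0.360/0.424 = 0.85 | 5.2% | 10.4% | 5.2% |
| milder decay | constant | 4.6% | 0.331/0.332 = 1.00 | 4.3% | 7.1% | 4.6% |
| milder decay | growing | 6.1% | 0.319/0.336 = 0.95 | 4.8% | 8.8% | 4.7% |
| milder decay | peak | 7.0% | 0.331/0.366 = 0.90 | 4.6% | 8.6% | 4.8% |

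A separate run of the same design with other assumed correlations agreed. The interaction test rejected 7.7-10.3%. Day 5 rejected 4.9-6.2% with constant post-baseline variance and about 8% with growing variance, against 4.2-5.3% for Day 5 ANCOVA.

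**The case against.** Four arguments narrow the point.

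*Only a random intercept?* A reader might infer that the model has nothing else. The article does not say so. A random intercept can be combined with a structured residual covariance, and an analysis plan that is not shown might add one. This stands as a limit: the figures above apply to default independent residuals. It does not remove the point, because the article commits to a named random structure and gives the same analysis a second label.

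*Are the standard errors wrong because correlations are equal?* That is tempting, but it fails for the primary outcome. With decaying correlation and constant SD, Day 5 rejection was 4.6%. The error there comes mainly from variance that differs by visit, and the article gives no SDs by visit. The entry criterion of NRS 5 or more does not settle it, because baseline enters as a covariate and its own truncated variance is not pooled into the residual.

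*Is the missing-data method therefore invalid?* Again the documents do not support this. A random-intercept model is a likelihood-based repeated-measures model and uses incomplete records under missing at random, so part of the contrast with MMRM is terminology. Its validity does need an adequate covariance, which is a reason to prefer a flexible one. The simulations above use complete data, and no bias from dropout has been quantified.

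*Are there safeguards already?* Section 2.11 plans ANCOVA on multiply imputed and last-observation-carried-forward data as sensitivity analyses. These could expose a Day 5 result driven by the covariance, but they would not replace the primary model. The largest inflation is also in the group-by-time test, which is not the primary contrast, and its size depends on which visits enter the model.

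**Conclusion.** The point holds as a specification that does not fit the schedule, together with two labels that need reconciling. With independent residuals and correlation that decays over time, the nominal 5% group-by-time test rejects about 7-10% under the null, against 4.7-5.7% when correlation really is equal. The Day 5 post-treatment contrast is about 5-6% if variance is constant over visits. If variance differs by visit it is about 6-9%, with a standard error 5-15% too small in the scenarios run. The unstructured equivalents stay at 4.0-5.5% throughout.

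The direction for the group-by-time test is secure wherever correlation falls with time. The exact sizes rest on assumed SDs, correlations and discharge timing. The planned 41 evaluable and 60 randomized per group are not affected.

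**What to change.** In Section 2.11, replace the random-intercept wording with one description of the primary model: an MMRM with categorical time, group, group-by-time, baseline and baseline-by-time, unstructured within-patient covariance and Kenward-Roger degrees of freedom. State that the primary test is the group contrast at Day 5 after treatment. Pre-specify the fallback if the model does not converge: heterogeneous Toeplitz, or the random intercept with robust standard errors.

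The cost is a few lines of text and code. The one real downside is size: nine post-baseline assessments need 9 × 10/2 = 45 covariance parameters with about 41 evaluable patients per arm. Table 1 also lets the discharge assessment stand in for Day 5 when the two coincide, so some patients will not have both values. The fallback may therefore be needed and should be fixed before the data are seen.

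### Beyond the baseline outcome, covariates enter the primary model by a baseline significance test, so the model is not fixed in advance and optional precision is given up; type I error and planned power are not harmed

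*Protocol article*

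**What the plan says.** Section 2.11 (Statistical methods) makes a linear mixed model with a random subject intercept the primary analysis. Its fixed effects are time, group, their interaction, the baseline outcome, and "clinically important covariant factors that are statistically significantly differ between groups at baseline as the covariates". The baseline outcome is therefore always in the model. Any other variable must pass two filters: it must be judged clinically important, and it must differ significantly between the arms at baseline. No candidate variables are listed.

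The same section describes the between-group baseline tests (t or Wilcoxon, chi-square or Fisher) and sets the significance level at .05 for all analyses. The sensitivity analyses of covariance, on the multiply imputed and last-observation-carried-forward data, are to be run "with the same covariates as those in the primary analysis".

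Section 2.8 describes block randomisation with random block sizes and states no stratification factors. Section 2.9 blinds only the assessor.

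**The concern.** Adjustment in a randomised trial is useful when a covariate predicts the outcome. The rule selects on something else. If randomisation is sound, a significant baseline difference is a chance event and does not show that the variable predicts pain on day 5. A strong predictor that happens to be balanced is left out, while a weak one that happens to differ, and is judged important, goes in.

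Three things follow.

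- The primary model cannot be written down until baseline data have been compared by arm.
- The clinical-importance filter has no definition and no stated time at which it is applied. That leaves discretion in a trial with a self-reported outcome and unblinded participants and physicians.
- The sensitivity analyses inherit the selected set, so they cannot show whether the selection mattered.

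This is a rule that the article states, not a detail left to an analysis plan. An analysis plan that followed the rule would have the same property.

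**Working it through.** **Inputs from section 2.7.** Two-sided alpha is 0.05. The stated power is "power at 90% to calculate the sample size"; the same sentence also gives beta as 0.2, which would mean 80%. Cohen's d "was 0.63, and the correlation between the baseline and endpoint measurements was assumed to be 0.5". The evaluable requirement is given as 41 in each arm, raised to 60 to allow for 30% withdrawal.

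**Step 1: reproduce the sample size.** With adjustment for the baseline outcome alone, the normal approximation is

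n per arm = 2 × ((1.960 + 1.282)/0.63)² × (1 − 0.5²) = 52.95 × 0.75 = 39.7, so 40.

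The noncentral-t version with 2n − 3 degrees of freedom gives 41 (power 0.902). At 80% power the result would be 30 or 31, so 41 matches 90%. For withdrawal, 41/0.70 = 58.6, so 59, against the stated 60. The sample size thus uses only the baseline outcome, which is always in the model.

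**Step 2: how often the rule would add something.** With k independent candidates tested at 0.05, P(at least one significant) = 1 − 0.95^k.

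| k (assumed) | Probability |
|---|---|
| 3 | 0.143 |
| 5 | 0.226 |
| 10 | 0.401 |

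The article does not give k. The clinical-importance filter would reduce the number of candidates.

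**Step 3: what a pre-specified list could add.** Let R² be the share of the variance remaining after the baseline outcome that the extra covariates explain. The documents give no value, so a range is shown. The residual variance is 0.75 × (1 − R²) and the standard error is multiplied by √(1 − R²). By normal approximation at 41 per arm and d = 0.63:

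| R² (assumed) | Reduction in SE | Power | n per arm for 90% |
|---|---|---|---|
| 0 (baseline outcome only) | – | 0.909 | 40 |
| 0.05 | 2.5% | 0.922 | 38 |
| 0.10 | 5.1% | 0.935 | 36 |
| 0.20 | 10.6% | 0.958 | 32 |
| 0.30 | 16.3% | 0.976 | 28 |

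**Step 4: how much of that the protocol's rule recovers.** Trials were simulated with an analysis of covariance at 41 per arm, d = 0.63 and correlation 0.5, with independent normal covariates. The rule was applied mechanically at p < 0.05.

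| Covariates, R² (assumed) | Power, protocol's rule | Power, pre-specified | Difference (points) |
|---|---|---|---|
| 2, 0.05 | 0.897 | 0.907 | 1.0 |
| 2, 0.10 | 0.907 | 0.921 | 1.4 |
| 3, 0.10 | 0.897 | 0.911 | 1.4 |
| 2, 0.20 | 0.902 | 0.948 | 4.6 |
| 3, 0.20 | 0.896 | 0.941 | 4.5 |
| 5, 0.20 | 0.904 | 0.935 | 3.1 |
| 3, 0.30 | 0.906 | 0.965 | 5.9 |

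In the three-covariate runs, adjusting for the baseline outcome alone gave 0.895, 0.892 and 0.896 at R² of 0.10, 0.20 and 0.30. The rule therefore recovers little of the available gain. With 6,000 trials, the Monte Carlo error of a power near 0.90 is √(0.9 × 0.1/6000) = 0.004, so the smallest differences are approximate.

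**Step 5: type I error.** With no treatment effect, the rule rejected in 0.037 to 0.050 of simulated trials, with the lowest value for the strongest covariates. It is not inflated and is slightly conservative.

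**The case against.** The strongest reply is that little is at stake. The covariate on which the sample size relies is pre-specified, 41 per group reproduces at 90% power, and type I error is held. The significance filter looks at baseline values and allocation, not at outcomes, so it cannot by itself steer the result towards a treatment effect. If more than 41 per arm are analysed, power with the baseline outcome alone rises, to about 0.98 at 60, and there is less to gain. All of this stands, and it limits the severity.

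The sizes also rest on assumptions. The article gives neither the number of candidates nor their prognostic strength. At R² of 0.05 the loss is about one power point.

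A reader might infer more than the documents support:

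- **That the trial becomes underpowered.** It does not. The loss is a gain that the plan never counted on.
- **That the rule produces false positives.** Applied mechanically, it does not. If someone instead chose the most favourable subset of the imbalanced variables after seeing results, simulated type I error was 0.054 to 0.059 (5 to 10 candidates, R² of 0.10 to 0.20), against about 0.050. That is a modest cost of unrestricted discretion, and nothing in the article says that the choice would be made that way.
- **That a variable affected by allocation will enter the model.** Section 2.11 compares treatment expectancy between groups, and Table 1 puts that questionnaire on day 2, the day of allocation. The order within the day is not stated, so this is only a possibility.

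The reply does not justify the rule. Selecting on chance imbalance has no advantage over a short fixed list, and the clinical-importance filter remains undefined.

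**Conclusion.** The point holds as a pre-specification weakness that should be fixed; it does not invalidate the design. The composition of the primary model beyond the baseline outcome depends on chance and on an undefined judgement, and the sensitivity analyses carry the same dependence. The forgone precision is worth about 1 to 6 power points at d = 0.63, correlation 0.5 and 41 per arm, for an assumed partial R² of 0.05 to 0.30. The simulations use a single-endpoint analysis of covariance as a stand-in for the mixed model. The targets of 41 evaluable and 60 randomised per group need no change on this account.

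**What to change.** In section 2.11, delete the baseline-significance criterion. Before any data are compared by arm, name one fixed list for the primary model and the sensitivity analyses: the baseline value of the outcome, plus one or two variables measured before randomisation and chosen for expected prognostic value. Keep them in the model whatever their observed balance.

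This takes one sentence, no extra patients and no extra data collection if the variables are among those already recorded at screening. The downside is one or two degrees of freedom, which is negligible with about 80 evaluable participants (2 × 41 = 82). If the chosen variables turn out to be weak predictors, the gain is small, but the primary model is still fixed in advance.
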